#### Secondary outcome measures

The following are the secondary outcome measures:
Mortality rate at 90 days.Cause of death (e.g., related to recurrence, a symptomatic complication post-surgery comorbidities).Modified Rankin Scale at 90 days (Table 1).Patient-reported health status assessed by the SF-36 questionnaire (during admission and at 90 days follow-up).Length of hospital stay (at the department of neurosurgery before discharge to home or transfer to another hospital).Complications related to the drain such as bleeding from the skin, pain, general discomfort, and infection will be monitored as long as the patients are admitted to the neurosurgical department, and therefore, the observation period can vary. Drain-related complications are not to be graded regarding severity, but as “yes or no.” Time (hours) of the onset of symptoms post-surgery will also be noted.Complications related to immobilization such as deep venous thrombosis and/or pulmonary embolism and brain infarction will be monitored as long as the patients are admitted to the neurosurgical department, and therefore, the observation period can vary. These complications will be noted as “symptomatic” or “asymptomatic.” The time (hours) of the onset of symptoms post-surgery will also be noted.Sub-analyses of patients with recurrence at 90 days: co-morbidities, medications, age, gender, and evaluation of hematoma subtypes on CT from admission (homogenous, separated, mixed, or membranous [2]).

**Table 1 Tab1:** Modified Rankin Scale (mRS)

mRS score	Description
0	No symptoms
1	No significant disability despite symptoms; able to carry out all usual duties and activities
2	Slight disability; unable to carry out all previous activities but able to look after own affairs without assistance
3	Moderate disability: requiring some help (e.g., with shopping/managing affairs) but able to walk without assistance
4	Moderately severe disability: unable to walk without assistance and unable to attend to own bodily needs without assistance
5	Severe disability; bedridden, incontinent, and requiring constant nursing care and attention
6	Dead

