#### Secondary outcomes

Mortality at 3 months will be analyzed by relative risk regression as with the primary outcome. SF-36, mRS, hours until mobilization, and length of hospital stay will be analyzed by linear or ordinal regression. The occurrence of different types of complications among the three study groups will be analyzed with a log-linear Poisson regression model.

For all secondary outcome measures, we investigate the superiority of each of the two experimental arms compared to the active control arm at the final analysis.

We use two-sided tests with a significance threshold of 0.05.

The data analysis will be an intention-to-treat analysis.

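### Yes/no drain-related complications are assigned a Poisson model with no robust variance stated; at its default variance the test is conservative and loses power for common complications

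*Protocol article*

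**What the plan says.** Two parts of the protocol article matter here.

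- **Outcomes {12}, Secondary outcome measures.** For the drain-related items (skin bleeding, pain, discomfort, infection): "Drain-related complications are not to be graded regarding severity, but as “yes or no". For the immobilization-related items: "These complications will be noted as “symptomatic” or “asymptomatic". Onset time is noted for both groups. Both are followed only during the stay in the neurosurgical department, and "therefore, the observation period can vary".
- **Statistical methods {20a}, Secondary outcomes.** For complications: "The occurrence of different types of complications among the three study groups will be analyzed with a log-linear Poisson regression model". For the other binary secondary outcome: "Mortality at 3 months will be analyzed by relative risk regression as with the primary outcome". For all secondary outcomes, "we investigate the superiority of each of the two experimental arms compared to the active control arm at the final analysis", and "We use two-sided tests with a significance threshold of 0.05".

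For complications, the text gives no variance estimator, offset, person-time or unit of analysis. The section on the choice of non-inferiority margin, by contrast, does name cluster-robust standard errors for the reanalysis of the meta-analysis.

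**The concern.** A Poisson model takes the variance of each observation to equal its mean, p. A yes/no value has variance p(1-p), which is smaller. With one yes/no value per patient, the Poisson point estimate of the risk ratio is sound. The default standard error is too large, however, and the gap grows with the risk.

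The Trial rationale section hypothesizes fewer drain-related complications with shorter drainage. If a shorter arm proves non-inferior on recurrence, these comparisons are part of the argument for adopting it. Pain and discomfort are the listed items most likely to be common, and they are where an oversized standard error would cost most. The plan already uses a model suited to binary data for recurrence and mortality, so a better-matched method is at hand.

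**Working it through.** **Inputs.** 724 per arm at the final stage, control rate 16.3%, margin 7%, final one-sided alpha 0.025 and final-stage power 0.95 (all from Sample size {14}). Two-sided 0.05 for secondary outcomes (Statistical methods {20a}). The protocol gives no complication risks, so a range is assumed.

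**Step 1: the plan's own sample size.** n = (1.960 + 1.645)² × 2 × 0.163 × 0.837 / 0.07² = 12.99 × 0.27286 / 0.0049 ≈ 724 per arm. This matches the protocol, so 724 is used below.

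**Step 2: standard error of the log risk ratio, one yes/no value per patient, no covariates.**

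- Default Poisson: sqrt(1/(n·p1) + 1/(n·p0))
- Binary (and robust): sqrt((1-p1)/(n·p1) + (1-p0)/(n·p0))

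With p1 = p0 = p, the ratio of the first to the second is 1/sqrt(1-p).

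**Step 3: actual level of the nominal 0.05 test.** Level = 2 × [1 - Φ(1.96/sqrt(1-p))]. At 20%: 1.96 × 1.118 = 2.19, which gives 0.028. The last two columns come from 200,000 simulated comparisons per risk at 724 per arm.

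| Assumed risk | SE ratio | Level, formula | Level, simulated, default Poisson | Level, simulated, robust |
|---|---|---|---|---|
| 5% | 1.026 | 0.044 | 0.042 | 0.047 |
| 10% | 1.054 | 0.039 | 0.038 | 0.049 |
| 20% | 1.118 | 0.028 | 0.028 | 0.049 |
| 30% | 1.195 | 0.019 | 0.019 | 0.049 |
| 40% | 1.291 | 0.011 | 0.011 | 0.051 |
| 50% | 1.414 | 0.006 | 0.005 | 0.049 |

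At 2% the two simulated levels are practically equal (0.0415 and 0.0417).

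**Step 4: power at 724 per arm.** For 30% versus 23%, |log RR| = ln(0.30/0.23) = 0.266. The binary SE is sqrt(0.70/217.2 + 0.77/166.5) = 0.0886. The default Poisson SE is sqrt(1/217.2 + 1/166.5) = 0.1030.

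- Binary: Φ(0.266/0.0886 - 1.96) = 0.85
- Default Poisson: Φ((0.266 - 1.96 × 0.1030)/0.0886) = 0.76

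| Assumed risks, 24 h vs shorter arm | Default Poisson | Binary/robust |
|---|---|---|
| 2% vs 1% | 0.33 | 0.34 |
| 5% vs 2.5% | 0.68 | 0.69 |
| 10% vs 6% | 0.77 | 0.79 |
| 20% vs 14% | 0.81 | 0.85 |
| 30% vs 23% | 0.76 | 0.85 |
| 50% vs 42% | 0.65 | 0.86 |

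**Step 5: check on fitted models.** With 36 versus 72 events out of 724 each, a Poisson fit gives p = 0.00068 with default variance and 0.00044 with robust variance. The intervals for the risk ratio are 0.335 to 0.746 and 0.340 to 0.736. With 7 versus 14 events the p-values are 0.134 and 0.132.

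**Step 6: if several types were summed per patient.** For four yes/no items with equal risk p and within-patient correlation ρ, variance/mean = (1-p)(1+3ρ). This exceeds 1, and the test becomes too liberal, only when ρ > p/(3(1-p)); at 20% risk that is 0.2/2.4 = 0.083. At 20% and ρ = 0.2 the ratio is 0.8 × 1.6 = 1.28 and the level is about 0.083. At ρ = 0 the ratio is 0.8 and the level is 0.028. The protocol gives neither the correlation nor any statement that types are summed.

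**The case against.** The strongest reply is that the text never says default variance is used. Poisson regression with robust variance is an accepted route to risk ratios for binary data, and an article may leave the estimator to an analysis plan that is not shown. It is true that default variance is an inference. But the model is a stated choice that differs from the one given to mortality in the same paragraph, and the article does name robust errors where it uses them. An analyst following the sentence as written would get the default.

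Two other readings would carry no such error. Because the observation period varies, a rate model is conceivable; but no offset or person-time is given. A log-linear model of the full arm-by-outcome table, including the patients without the complication, would match logistic regression. With assumed counts of 181/724 and 217/724, both give a coefficient of -0.250, SE 0.118 and p = 0.034. That reading is possible, but nothing in the text sets it out.

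Yes/no coding is explicit only for drain-related items. That limit stands.

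A reader might infer that the p-values and intervals are generally wrong, or that a chance difference could too easily be declared a benefit. The document does not support this. Analysed by type, the test is conservative. The liberal direction needs types summed within patients and enough within-patient correlation. The protocol states neither, and its reference to different types points rather to separate analyses.

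**Conclusion.** The point holds in limited form. The stated model does not match yes/no data. Fitted per type with its default variance, it makes the complication comparisons conservative. The loss is about 2 points of power at 10% versus 6%, about 9 points at 30% versus 23% and about 21 points at 50% versus 42%. It is about 1 point at 5% versus 2.5%, so for rare events the matter can be ignored.

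This rests on four assumptions: assumed complication risks, one yes/no value per patient and type, default variance, and both compared arms reaching 724 without centre adjustment. The actual levels in the formula column depend only on the risk and not on the sample size. Recurrence, the non-inferiority tests and the arm-dropping decisions are not affected.

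**What to change.** In Statistical methods {20a}, Secondary outcomes, replace the complication sentence with wording to this effect:

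- Each drain-related complication type is analysed as one yes/no value per patient, with the same centre-adjusted relative risk regression as recurrence and mortality.
- If that model does not converge, Poisson regression with robust (sandwich) variance is used, with tests and intervals taken from that variance.
- If types are combined, the outcome is any complication per patient, or the robust variance is clustered on patient.
- The occurrence of immobilization-related complications is handled in the same way, with the symptomatic/asymptomatic label described separately.

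The cost is a few lines of wording. No new data, patients or procedures are needed. The interim analyses section reserves secondary outcomes for the final analysis, so the change can be made before any complication comparison is seen.

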### Interim analyses {21b}

Interim analyses of the primary outcome will be conducted at the end of each stage (see the “Sample size {14}” section). The early dropping of an experimental arm (6 or 12 h of drainage) can be chosen if stage-specific significance is not achieved by the respective arm. Secondary outcome measures will only be considered during the final analysis.

### Methods for additional analyses (e.g., subgroup analyses) {20b}

Patients with CSDH recurrence at 90 days will be considered separately. Descriptive tables of CT-based hematoma subtypes, frequency of comorbidities, medications, gender, and descriptive summaries of patient age will be created.

### Methods in analysis to handle protocol non-adherence and any statistical methods to handle missing data {20c}

Loss to follow-up is expected to be rare, and analyses will be done as complete case analyses. All outcomes will be analyzed using intention-to-treat analyses. For the primary outcome, this will be supplemented by an as-treated sensitivity analysis in which the observed drainage times will be used as a continuous covariate instead of the randomly assigned drainage times.

### Plans to give access to the full protocol, participant-level data, and statistical code {31c}

We have no plans for granting public access to the protocol, dataset, or statistical code.

### Oversight and monitoring

#### Composition of the coordinating center and trial steering committee {5d}

**Principal investigator:**
Preparation of protocol and revisionsPreparation of written patient informationApplying for ethical approvalOrganizing steering committee meetingsPublication of study reportsMember of steering committee DACSUHS

**Steering committee** (see title page for all members):
Agreement of final protocol.All investigators will be steering committee members; one lead investigator per department will be nominated as the local coordinator.Recruitment of patients.Reviewing the progress of the study and, if necessary, agreeing on changes to the protocol.Data verification.Randomization.

**Data manager:**
External, independent person from OPENMaintenance of the trial IT system (REDCap)Monitoring of all activity in the REDCap systemData verification

#### Person responsible for data monitoring

An external, independent biostatistician will perform all the statistical analyses throughout the study.

#### Composition of the data monitoring committee, its role, and reporting structure {21a}

A data monitoring committee (DMC) is not established. The decision was because of a relatively simple study design and with potentially minimal risk. The study has a well-described statistical plan that also describes when the interim analyzes should take place and that early dropping of an experimental arm can be chosen if stage-specific significance is not achieved by the respective arm.

However, an external, independent biostatistician will monitor the study data and will be responsible for all the statistical work. The biostatistician is blinded and independent of the study organizers. During the period of recruitment to the study, interim analyses will be supplied together with any other analyses that the research steering committee (DACSUHS) may request. In the light of these interim analyses (three interim analyses and one final analysis), the biostatistician will advise the steering committee based on the previously defined stopping guidelines.

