### Trial design {8}

The DRAIN-TIME 2 study is a Danish multi-center, national randomized controlled non-inferiority trial with three parallel arms. The arms correspond to 6, 12, and 24 h of drainage, where the former two arms are experimental and the 24 h group is the common control arm. Online randomization with a 1:1:1 allocation will be performed.

The trial uses a multi-arm, multi-stage (MAMS) design, which enables adaptive reductions of the number of experimental arms considered during the trial, with the aim to lower the required sample size on average. The applied design is described in Bratton et al. [6]. Our trial is organized into five stages. After each stage, non-inferiority of both arms is tested during an interim analysis at stage-specific significance levels. Significant arms continue to the next stage, whereas non-significant arms can be dropped (non-binding).

The final non-inferiority test decision is taken after the final stage (or as soon as both experimental arms are stopped) and uses all available data. Interim and final analyses rely on the same primary outcome and the same non-inferiority margin.

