## Statistical methods

### Statistical methods for primary and secondary outcomes {20a}

#### Primary outcome

Recurrence will be treated as a binary outcome (instead of a time-to-event outcome) due to the time to recurrence being of minor clinical interest compared to the occurrence of the event itself which is of major clinical relevance. As an effect measure, we consider relative risks due to their natural interpretability.

We will use relative risk regression with treatment assignment (6 h vs. 12 h vs. 24 h drainage time) as a categorical covariate and take the different trial centers into account. Adjusted risk ratios with 95% confidence intervals for recurrence rate will be reported. We investigate a non-inferiority hypothesis with a non-inferiority margin of 7% (see the “Sample size {14}” section). We will make two comparisons—one for each experimental arm (6 and 12 h) versus the common control arm (24 h) using likelihood ratio tests. We will use a one-sided test together with stage-specific significance thresholds equaling 0.5, 0.3, 0.2, 0.1, and 0.025 for each of the five stages.

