#### Adverse event reporting and harms {22}

An interim analysis is performed as illustrated in the “Sample size {14}” section. If one of the arms is associated with a higher recurrence rate, death, or any other unexpected adverse effect, the steering committee will decide what precautions are to be made.

Otherwise, the operations and postoperative care and handling all follow standard procedures.

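### The oversight section counts three interim analyses where the five-stage design has four, and the interim section reserves for the final analysis the deaths on which the harms section expects action; access to by-arm interim results also needs a limit

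*Protocol article*

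**What the plan says.** **Number of looks.** Trial design {8} states "Our trial is organized into five stages" and "After each stage, non-inferiority of both arms is tested during an interim analysis at stage-specific significance levels". The sample-size table gives five cumulative sizes per arm (91, 182, 344, 477, 724). The primary-outcome analysis uses "stage-specific significance thresholds equaling 0.5, 0.3, 0.2, 0.1, and 0.025 for each of the five stages", and Interim analyses {21b} places an analysis at the end of every stage. The section on the data monitoring committee {21a} instead reads: "In the light of these interim analyses (three interim analyses and one final analysis), the biostatistician will advise the steering committee".

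**Deaths and harms.** Outcomes {12} lists 90-day mortality and the complications as secondary outcomes. Interim analyses {21b} says "Secondary outcome measures will only be considered during the final analysis". Adverse event reporting and harms {22} starts from the interim analysis and has the steering committee decide on precautions "If one of the arms is associated with a higher recurrence rate, death, or any other unexpected adverse effect". No data monitoring committee is set up.

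**Access to results.** Section {21a} adds that "interim analyses will be supplied together with any other analyses that the research steering committee (DACSUHS) may request". Under the committee's composition {5d}, "All investigators will be steering committee members", and its listed tasks include recruitment and randomization.

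**The concern.** Section {21a} governs what the independent biostatistician delivers, and its count does not fit the design that produced the sample size. It does not say which look would be missing. If a look were skipped, an inferior arm would tend to be dropped later and more patients would be randomised than the plan states.

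The interim and harms sections cannot both be followed as written. The harms section expects the interim to show whether an arm has more deaths or other unexpected adverse effects, while the interim section limits that analysis to recurrence. With no monitoring committee, no scheduled analysis fills the gap.

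The third part is a design weakness. Allocation is open from 6 h, and the primary endpoint includes a judgement that reoperation is needed. Investigators who knew interim recurrence by arm could be influenced in enrolment or in that judgement.

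**Working it through.** **1. Count of looks.** Five stages, each ending in a test, with the fifth being the final one: 5 − 1 = 4 interim analyses plus 1 final. Section {21a} has 3 + 1 = 4 analyses in all, which is a four-stage trial.

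**2. Does the stated design need four interim looks?** Inputs from Sample size {14}: recurrence 16.3% in all arms, margin 7% on the risk difference, 1:1:1 allocation, one-sided stage levels 0.5, 0.3, 0.2, 0.1, 0.025, and stage powers 0.9 (stages 1 to 3) and 0.95 (stages 4 and 5).

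Size per arm at a stage: n = 2p(1 − p)(z₁₋α + z_power)² / 0.07², with p = 0.163, so 2p(1 − p) = 0.2729.

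| Stage | α | Power | Computed n | Stated n |
|---|---|---|---|---|
| 1 | 0.5 | 0.90 | 91.5 | 91 |
| 2 | 0.3 | 0.90 | 181.6 | 182 |
| 3 | 0.2 | 0.90 | 251.0 | 344 |
| 4 | 0.1 | 0.95 | 476.9 | 477 |
| 5 | 0.025 | 0.95 | 723.6 | 724 |

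Stages 1, 2, 4 and 5 reproduce. The stage 3 figure of 344 corresponds to a power of 0.95 (344.3), not the stated 0.9. That is a separate matter; the tabulated 344 is used below.

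The operating characteristics were simulated (400,000 runs): three binomial arms at the tabulated sizes, an unpooled Wald non-inferiority test at each stage level, stopping guidelines followed, and the control arm recruiting while any experimental arm continues. Inferior means a recurrence of 16.3% + 7% = 23.3% in both experimental arms.

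| Interim looks | Expected N, both inferior | Expected N, both non-inferior | Power per comparison | Familywise error |
|---|---|---|---|---|
| Stated in the protocol | 690 | 1928 | about 0.8 | about 0.028 |
| All four | 696 | 1942 | 0.805 | 0.028 |
| Stage 1 left out | 849 | 2024 | 0.849 | 0.030 |
| Stage 2 left out | 850 | 1996 | 0.839 | 0.031 |
| Stage 3 left out | 755 | 1951 | 0.813 | 0.029 |
| Stage 4 left out | 756 | 1949 | 0.814 | 0.031 |

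With four looks all the stated figures reproduce (696 and 1942 lie within 1% of 690 and 1928). With any one look left out, 690 does not. Compared with the simulated four-look value, the excess is 755 − 696 = 59 to 850 − 696 = 154 patients.

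The pairwise error is 0.015 to 0.016 when the guidelines are followed and about 0.025 when they are ignored, whichever look is missing. This is expected: an interim look can only drop an arm, so removing one gives both good and bad arms fewer chances to be dropped.

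**3. Deaths at the interim.** Mortality is a secondary outcome {12}; secondary outcomes belong to the final analysis only {21b}; the harms section acts on death after an interim analysis {22}. The scheduled interim therefore cannot contain what the harms section needs. The one route left is an optional request by the steering committee under {21a}, which is unscheduled, tied to no rule, and itself at odds with {21b}.

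**4. Access.** Read together, {21a} and {5d} send interim analyses to a body that includes every investigator, with no stated limit on by-arm detail. No arithmetic applies, and the document gives nothing from which a bias could be sized.

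**The case against.** **Look count.** The phrase in {21a} is a parenthesis in an oversight section that defers to stopping guidelines defined elsewhere, and it is most likely a miscount. That stands. A reader might infer that one threshold has no scheduled analysis, but the primary-outcome and interim sections schedule all five. A reader might also infer lost power or inflated error. The calculation shows that power goes up and the error rates barely move.

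**Mortality.** A reader might infer that excess deaths would go unseen until as many as 2172 patients had been randomised. The text does not support this. The biostatistician monitors the study data, the committee may request other analyses and meets after each interim, allocation is open after 6 h, and 2172 assumes that no arm is dropped. What survives is narrower: no scheduled analysis compares deaths by arm, and two sections disagree on whether the interim covers them.

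**Access.** A reader might infer that by-arm results do go to all investigators. Section {21a} says only that analyses are supplied and advice is given; it does not say whether the committee sees by-arm results, masked results or a recommendation. The endpoint also requires neurological deterioration leading to hospitalization and recurrence confirmed on imaging, which limits the scope for a shifting reoperation threshold. This part is therefore an inferred risk and not a contradiction.

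**Conclusion.** Two contradictions hold. The interim count in {21a} is wrong against every section that defines the design. Its statistical cost, if followed, is a later drop of inferior arms (expected size about 755 to 850 instead of 690, depending on which look is missing), with no loss of power and a pairwise error still at or below 0.025. These figures assume the tabulated stage sizes, a Wald test on the risk difference and adherence to the stopping guidelines.

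The interim and harms sections conflict on death and other adverse effects, which leaves no scheduled by-arm comparison before the final analysis. Its consequence cannot be sized from the document.

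The open channel from the biostatistician to the investigators is a lower-confidence design concern, because the level of detail supplied is unstated.

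**What to change.** 1. In {21a}, change the count to four interim analyses and one final analysis. This costs one word.
2. In {21b}, state that each interim report contains a descriptive by-arm table of all-cause mortality and of the adverse effects that {22} covers, and that efficacy testing of secondary outcomes stays with the final analysis. This costs one extra table per report.
3. In {21a}, state that the independent biostatistician routinely sends the steering committee only a continue-or-drop recommendation for each arm, that by-arm recurrence results stay closed until the final analysis, and that by-arm safety data are released only when {22} requires a decision. The clause on requested analyses need not be deleted, only made subject to these limits. The cost is that the committee loses routine access to interim results and, with no monitoring committee, one statistician holds the by-arm safety data between decisions.
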